**Fig. 2 Fig2:**
[figure not shown]
Flowchart of the study design, including enrollment, allocation, and follow-up assessments

### Randomization procedure

People willing to participate and fulfilling the eligibility criteria will be randomized (1:1:1 allocation ratio) after baseline assessment. A priori, an independent statistician will prepare a computer-generated randomization schedule in randomized, permuted blocks of four or six persons.

### Interventions

Participants will be randomized to one of three groups. The first group will receive a 6-month multicomponent lifestyle intervention combining physical activity, diet, a progress journal, and health behavior change workshops. The second group will receive the same lifestyle intervention together with a structured sleep intervention. The third group, serving as the control, will receive standard lifestyle recommendations for physical activity and diet in order to limit deception bias.

#### Lifestyle intervention

Participants randomized to the lifestyle group will participate in a 6-month multicomponent lifestyle intervention. The intervention is informed by Self-Determination Theory and the affectivism approach. The specific components of the physical activity program, the associated behavior change techniques (BCTs) [30], and theoretical constructs are summarized in the additional files [see Additional File 2].

#### Progress journal

At the start of the intervention, participants will be provided with a progress journal to support participant-centered goal setting and behavior tracking throughout the six-month program. This journal includes key information about the lifestyle program. The journal contains an overview of the lifestyle intervention, a weekly physical activity diary for planning and self-monitoring, and sections to identify potential barriers and facilitators. Together with their Adapted Physical Activity (APA) instructor, participants will co-develop weekly challenges aimed at reducing sedentary behavior and/or increasing physical activity.

#### Physical activity component

Participants will be referred to an APA teacher for an individualized 6-month exercise program. The program includes up to 20 supervised sessions (90 min each), combining aerobic and resistance training. On non-supervised days, participants will be encouraged to engage in additional exercise to meet the World Health Organization (WHO) physical activity guidelines (≥ 150 min of moderate-to-vigorous aerobic physical activity and 2 resistance training sessions per week) [1]. Physical activity levels will be objectively monitored throughout the intervention using a wearable device (Withings ScanWatch Light, Withings, France).

#### Diet component

Participants will attend five individual consultations (~ 45 min each) with a registered dietitian. Recommendations will follow French national public health guidelines and be tailored to individual needs and preferences. At the first consultation, the dietitian will conduct a dietary history using a structured checklist to assess usual intake. Food models and metric utensils will be used to estimate portion sizes. Supporting written resources will be provided, including healthy eating guidelines, shopping lists, meal plans, and recipes.

Consultations may address label reading, mindful eating, and food access considerations, depending on participant needs. At each consultation, participants will set personalized goals and discuss barriers and facilitators. The final session will review progress and establish strategies for long-term dietary change.

#### Health-behavior change workshops

Participants will be invited to attend three group-based health behavior change workshops (90 min each) focusing on physical activity and nutrition. The workshops aim to strengthen knowledge about physical activity, sedentary behaviors, and nutrition; explore perceptions of eating patterns; and support participants in setting and planning achievable goals for both physical activity and diet. They also encourage reflection on motivations, strategies to overcome challenges, and the identification of healthy eating behaviors to promote sustainable lifestyle changes.

#### Lifestyle and sleep intervention

Participants randomized to the lifestyle and sleep group will receive the 6-month lifestyle intervention described above, in addition to a structured sleep intervention. The sleep component was developed collaboratively by sleep researchers, certified sleep medicine specialists, and health behavior experts, and is grounded in the Theory of Planned Behavior (TPB) and the Health Action Process Approach (HAPA).

At baseline, a sleep specialist will review participants’ responses to validated questionnaires (Pittsburgh Sleep Quality Index, Epworth Sleepiness Scale, Insomnia Severity Index, Berlin Questionnaire, Horne and Ostberg questionnaire), together with their sleep diary and actigraphy-derived sleep–wake patterns. If further clinical assessment is indicated, participants will be referred for a consultation with a sleep specialist, in collaboration with their general practitioner.

All participants in this group will receive a sleep health program consisting of five individual 30-minute sessions with a trained facilitator. Sessions will cover evidence-based recommendations from the French Institute of Sleep and Vigilance, including: sleep duration and health outcomes, sleep hygiene practices, relationships between sleep and physical activity, and common sleep myths.

Participants will be supported in goal setting and self-monitoring of their sleep behaviors, using both their progress journal and an under-mattress sleep analyzer (Withings Sleep Analyzer, France). Each session will include review of progress, discussion of barriers, and collaborative development of specific, measurable goals for the following period. Examples include regularizing bedtimes, reducing bedroom technology use, or practicing relaxation techniques.

The details of the theoretical framework and the BCTs incorporated in the sleep intervention are summarized in the additional file (see Additional File 2).

#### Control group

Participants randomized to the control group will receive standard lifestyle recommendations (physical activity, diet) in order to limit deception bias.

### Outcomes

#### Primary outcome

The study has two primary outcomes, assessed 6 months after randomization:Steps per day, measured objectively using an Actigraph GT3X accelerometer (Actigraph Corp, USA). Steps per day were chosen because increases in daily step count are strongly associated with reduced all-cause mortality [31]. Furthermore, step count is passively tracked by widely used consumer technologies (e.g., smartphones), giving it practical relevance. Recent dose–response evidence also provides insights to inform future physical activity guidelines [32].Health-related quality of life, measured with the EQ-5D-5L questionnaire. This instrument is a widely used, cognitively simple, self-administered measure that assesses five dimensions of health (mobility, self-care, usual activities, pain/discomfort, anxiety/depression), each rated on five severity levels, along with a visual analog scale (EQ-VAS) for overall health [33]. Quality of life was selected as a co-primary outcome because self-rated health and health-related quality of life are robust predictors of mortality and chronic disease risk, and are sensitive to changes in lifestyle behaviors.

### Secondary outcomes

A range of secondary outcomes will also be assessed at baseline and different study timepoints (see Table 2).

**Table 2 Tab2:** SPIRAL+ Study Data Collection and Outcome Measures

Variable	Instrument	Baseline (T0)	Follow-up visit (2 weeks)	End of intervention (26 weeks)	12-month Follow-up (52 weeks)
Anthropometric & clinical data					
Waist, weight, height, BMI, blood pressure	Height to nearest 0.1 cm. Body weight to nearest 0.1 kg. BMI = weight divided by height squared kg/m^2^ Resting BP with sphygmomanometer	⎫		⎫	⎫
Body composition	Bio-electrical impedance	⎫		⎫	⎫
Device-measured physical activity	Actigraph GT3X	⎫		⎫	⎫
Device-measured sedentary time	Actigraph GT3X				
Device-measured sleep	Actigraph GT3X	⎫		⎫	⎫
Sleep	Sunrise sleep device	⎫		⎫	
Cardiorespiratory fitness	VO_2peak_	⎫		⎫	
Handgrip strength	Dynamometer	⎫		⎫	⎫
Self-report (questionnaires)					
Health-related quality of life	EQ-5D-5 L	⎫		⎫	⎫
Self-reported physical activity	Global Physical Activity Questionnaire (GPAQ)	⎫		⎫	⎫
Diet quality	Cardiovascular Diet Questionnaire (CDQ-2)	⎫		⎫	⎫
Sleep quality	Pittsburgh Sleep Quality Index (PSQI)	⎫		⎫	⎫
Quality of life	Quality of life SF-36	⎫		⎫	⎫
Wellbeing	Warwick–Edinburgh Mental Wellbeing Scale (34)	⎫		⎫	⎫
Sleepiness	Epworth Sleepiness Scale	⎫		⎫	⎫
Insomnia symptoms	Insomnia Severity Index	⎫		⎫	⎫
Chronotype	Horne Ostberg Morning Eveningness Questionnaire	⎫		⎫	⎫
Motivation	Motivation Scale towards Health-Oriented Physical Activity (EMAPS)	⎫		⎫	⎫
Preference for and tolerance of exercise intensity	Preference for and Tolerance of Exercise Intensity Questionnaire	⎫		⎫	⎫
Attitude self-efficacy subjective norms and intention	Attitude self-efficacy subjective norms and intention	⎫		⎫	⎫
Vitality	Subjective vitality	⎫		⎫	⎫
Physical Activity Regulation	The Physical Activity Regulation Scale			⎫	
Competence, autonomy, relatedness	The Basic Need Satisfaction Scale			⎫	
Behaviors of the APA teacher	The Interpersonal Behaviors Questionnaire			⎫	
Implementability of the interventions	Acceptability, fidelity, feasibility			⎫	
Program adherence	The number of APA/diet/health-behavior workshops and sleep sessions attended, divided by total number of sessions			⎫	

### Clinical and paraclinical parameters

#### Cardiopulmonary exercise test

All participants will perform a graded maximal exercise test to determine peak O_2_ uptake (VO_2_) and parameters to guide aerobic exercise prescription. Participants will pedal on a cycle ergometer and wear a mouthpiece and nose-clip that permits breath-by-breath measurement of minute ventilation, O2 uptake and CO_2_ production from expired gas. Power output is increased every minute until the patient indicates either that he/she would like to stop, a physiological maximum is achieved (indicated by heart rate, BP, respiratory exchange ratio or VO_2_ plateau) or abnormalities appear that necessitate discontinuation. Work rate, heart rate, electrocardiogram and blood pressure data will be collected.

#### Body composition

Body composition will be determined using bioelectrical impedance. Bioelectrical impedance analysis is a method for estimating body composition, in particular body fat and muscle mass, where a weak electric current flows through the body and the voltage is measured in order to calculate impedance (resistance and reactance) of the body. Bioelectrical impedance will be measured using a bioelectrical impedance spectrum analyser (SFB7, Impedimed, Impedimed Ltd.).

#### Handgrip test

The purpose of the handgrip strength test is to measure the maximum isometric strength of the hand and forearm muscles. The participant holds the dynamometer in the hand to be tested, with the arm at right angles and the elbow by the side of the body. The handle of the dynamometer is adjusted if required - the base should rest on the first metacarpal (heel of palm), while the handle should rest on middle of the four fingers. When ready the participant squeezes the dynamometer with maximum isometric effort, which is maintained for about 5 s. No other body movement is allowed. The participant is be strongly encouraged to give a maximum effort. Three repetitions are performed, each separated by a 30-second rest period, and the best value is retained for analysis.

### Physical activity, sedentary behavior and sleep

Baseline physical activity and sedentary time will be evaluated with an Actigraph monitor (Actigraph GT3X, Actigraph Corp). Patients will be equipped with a research-grade activity monitor and will be asked to wear it for 7 days. The Actigraph is a small (5.1 × 4.1 × 1.5 cm), light (0.042 kg) instrument that records integrated acceleration information as an activity count, which provides an objective estimate of the intensity of body movements. The device is programmed to record in 1-minute epochs. Participants will be instructed to wear the monitor on their non-dominant wrist during all waking hours. However, because the monitors are not waterproof, participants are asked to take them off while bathing or swimming. They will also complete a sleep diary in order to indicate time in bed and time out of bed.

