**Methods:**

The SPIRAL+ study is a single-center, randomized controlled trial conducted in France, among non-exercising adults aged 18–80 years. Participants (*n* = 201) will be randomized to one of three groups: (1) lifestyle intervention (physical activity and diet) (2), lifestyle plus sleep intervention, or (3) control. Assessments will be conducted at baseline, 6 months (post-intervention), and 12 months. The primary outcomes are health-related quality of life (EQ-5D-5 L) and daily step count (measured by accelerometer) assessed immediately after the 6-month intervention. Secondary outcomes include whether intervention effects are sustained at 12 months, along with markers of physical fitness (cardiorespiratory fitness, body composition, handgrip strength), physical activity and sedentary behavior (accelerometry), and sleep (home-based sleep test, actigraphy, and validated questionnaires). Additional self-reported outcomes will cover diet, mental wellbeing, motivation, quality of life, and psychological constructs related to health behavior change. A qualitative component will explore barriers and facilitators to adherence through semi-structured interviews.

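### The Actigraph is to be worn during waking hours, yet it is the listed instrument for device-measured sleep at baseline, 26 and 52 weeks

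*Protocol article*

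**What the plan says.** All references are to the protocol article.

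- **Physical activity, sedentary behavior and sleep.** Participants receive an Actigraph GT3X and "will be asked to wear it for 7 days". The wear rule is: "Participants will be instructed to wear the monitor on their non-dominant wrist during all waking hours". The only removal mentioned is that "because the monitors are not waterproof, participants are asked to take them off while bathing or swimming". Alongside the monitor, "They will also complete a sleep diary in order to indicate time in bed and time out of bed".
- **Secondary outcomes, Table 2.** The row "Device-measured sleep" names the Actigraph GT3X and is marked at baseline, 26 weeks and 52 weeks. A separate row, "Sunrise sleep device", is marked at baseline and 26 weeks only.
- **Abstract, Methods.** The secondary outcomes include "sleep (home-based sleep test, actigraphy, and validated questionnaires").
- **Lifestyle and sleep intervention.** At baseline a sleep specialist reviews questionnaires and a sleep diary together with "actigraphy-derived sleep–wake patterns".

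**The concern.** A monitor worn only while the participant is awake records no movement during sleep. The article therefore lists an outcome that its own wear instruction does not allow to be measured. This is not a detail left to a fuller document: the article gives an explicit instruction, and that instruction does not fit the outcome table. No analysis plan could repair it, because nights that were not recorded cannot be analysed.

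The point matters because sleep is the component that separates the two active arms. Sleep quality and duration are named among the secondary objectives. The Discussion presents combined objective and subjective measurement of sleep as a methodological strength, and the 12-month visit as the means of judging whether behavior change lasts. The Actigraph is the only device listed for sleep at that visit.

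**Working it through.** No formula applies and the article gives no figure to reproduce. The check sets the passages side by side.

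1. **Is overnight wear requested anywhere?** No. The only wear instruction is the one quoted, and it refers to waking hours. The section opens with baseline measurement, and no different instruction is given for follow-up, so I take it to hold at all three assessments.

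2. **What could be derived under that instruction?** Step count and sedentary time could. Sleep onset, wake after onset, sleep efficiency and actigraphic sleep duration could not, since all need a recording during the sleep period. Diary times, or the gap when the device is off, would remain; neither is device-measured sleep.

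3. **What does this remove from the schedule?** Counting device-by-visit sleep measures in Table 2:
   - Planned: Actigraph 3 (baseline, 26, 52 weeks) + Sunrise 2 (baseline, 26 weeks) = 5.
   - Obtainable as written: Actigraph 0 + Sunrise 2 = 2.
   - At 26 weeks: 2 planned, 1 obtainable (Sunrise).
   - At 52 weeks: 1 planned, 0 obtainable.

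4. **Could another device fill the gap at 52 weeks?** Not on the article's description. The under-mattress analyzer is given to the lifestyle and sleep group for self-monitoring, so it offers no comparison between arms. The wearable used in the lifestyle program is described for physical activity, during the intervention.

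5. **What is untouched?** Both primary outcomes are assessed at 6 months. Steps per day does not need night wear, and EQ-5D-5L does not use the device. The Pittsburgh Sleep Quality Index, Insomnia Severity Index and Epworth Sleepiness Scale are marked at baseline, 26 and 52 weeks.

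6. **What else depends on night data?** The baseline review by the sleep specialist is said to use actigraphic sleep–wake patterns. Under waking-hours wear that input would be missing, and only the questionnaires and diary would be available.

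**The case against.** The strongest reply is that this may be a slip of wording. The section never tells participants to take the device off at bedtime, and bathing and swimming are the only removals it names. Its heading includes sleep. The diary of bed times is the usual companion to sleep actigraphy, and the description of the sleep intervention pairs the two. The waking-hours phrase may have been written with physical activity and sedentary time in mind. On this view round-the-clock wear is the practice and no data are lost.

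That is plausible, and it limits what can be claimed: the article does not show that any night has been missed. It does not remove the point. The bathing exception fits waking-hours wear equally well, and if nights are covered in practice, the sentence is wrong and needs correcting.

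A reader might also infer that the trial could not show objectively whether sleep changed, or that a primary result could not be traced to sleep. The documents do not support this. The Sunrise test gives an objective, repeated sleep measure at baseline and 26 weeks, the latter being the visit at which the primary outcomes are assessed. The article states no mediation objective, so tracing the primary result to sleep is not a standard the trial set itself.

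**Conclusion.** The article contradicts itself. Read literally, its wear instruction yields no Actigraph sleep data at any of three planned assessments and leaves no objective between-arm sleep measure at 52 weeks. It also leaves the baseline sleep review without one of its stated inputs. The loss is confined to one secondary measure; the primary outcomes, objective sleep at 26 weeks and the sleep questionnaires stand.

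The size rests on two assumptions: that participants follow the instruction as written, and that the same instruction applies at every assessment. If 24-hour wear is already the practice, the loss is nil and the matter is a correction of text. The document cannot settle which case applies. Recruitment began in May 2024, so if waking-hours wear has been the practice, some nights may already be beyond recovery.

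**What to change.** First establish what participants have actually been told, then reconcile the wear instruction with Table 2, the abstract and the description of the baseline sleep review.

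- **If 24-hour wear is the practice:** correct the sentence to 7 days and nights, with removal only for bathing or swimming. This costs one line.
- **If waking-hours wear has been the practice:** extend the instruction to nights in all three arms at every remaining assessment and record the date of change. Report Actigraph sleep only for assessments with night wear, and change from baseline only where both assessments have it. The cost is a slight extra wear burden and incomplete Actigraph sleep data for participants assessed before the change.
- **If night wear will not be introduced:** remove the Actigraph sleep outcome from Table 2 and the abstract, and the reference to actigraphic sleep–wake patterns from the baseline review. The article should then make clear that objective sleep measurement ends at 26 weeks.

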#### Home sleep test

Sleep will be evaluated using a disposable medical device that is non-invasive and has CE marking (class IIa, under the European Directive 93/42/CEE). This device is developed by SUNRISE SA, and can be used in the home. The device is based on an automated mandibular jaw movement analysis (Sunrise, Namur, Belgium). It comprises a single point of contact sensor weighing 3 g that is attached to the *mentolabial sulcus* of the individual. It includes an embedded inertial measurement unit that records the rotational movement of the mandible using a gyroscope and the position of the mandible using an accelerometer. The sensor communicates with a smartphone application for external control and enables mandibular jaw movement data transfer overnight via Bluetooth. Recorded raw data is then transferred to a cloud-based infrastructure at the end of the night using a secured data protocol, where it is pre-processed and automatically analyzed by a machine learning-based algorithm.

### Questionnaires

Participants will complete validated questionnaires covering physical activity, sleep, diet, wellbeing, and motivational/psychological constructs, including: 
*Global Physical Activity Questionnaire (GPAQ)*: The GPAQ is a questionnaire developed by the World Health Organization (WHO) to assess physical activity levels in diverse populations. It measures physical activity across three domains: Work-related activity (occupational or domestic tasks, Travel-related activity (walking or cycling for transportation), Leisure-time activity (exercise, sports, or recreational activities). The GPAQ also captures sedentary behavior and provides data on the frequency, intensity, and duration of activities.
*Pittsburgh Sleep Quality Index (PSQI)*: The PSQI is a self-reported questionnaire that assesses sleep quality and quantity in terms of seven components, namely, subjective sleep quality, sleep latency, sleep duration, habitual sleep efficiency, sleep disturbances, use of sleeping medications, and daytime dysfunction (Buysse, Reynolds, Monk, Berman, & Kupfer, 1989).
*Warwick–Edinburgh Mental Wellbeing Scale (WEMWS).* This WEMWS is a 14-item scale of positively worded statements covering feeling and functioning aspects of mental wellbeing [34]. The 14-statements have five response categories from ‘none of the time’ to ‘all of the time’.
*Epworth Sleepiness Scale (ESS)*: The ESS measures daytime sleepiness and consists of eight items (situations) where individuals assess how likely they would fall asleep [35].
*Berlin questionnaire*: The Berlin questionnaire is a self-administered questionnaire that was developed to identify subjects with obstructive sleep apnea (OSA) in primary care settings [36].
*Horne Ostberg Morning Eveningness Questionnaire (MEQ)*: The MEQ consists of 19 items and was developed to assess individual differences in morningness and eveningness – the degree to which respondents are active and alert at certain times of day. Scale items query preferences in sleep and waking times, and subjective “peak” times at which respondents feel their best.
*Insomnia Severity Index (ISI)*: The ISI is a 7-item self-report questionnaire assessing the nature, severity, and impact of insomnia [37]. The dimensions evaluated are: severity of sleep onset, sleep maintenance, and early morning awakening problems, sleep dissatisfaction, interference of sleep difficulties with daytime functioning, noticeability of sleep problems by others, and distress caused by the sleep difficulties.
*Quality of life (SF-36)*: The Medical Outcomes Study 36-item Short-Form Health Survey (SF-36) is a widely used, generic, patient-report measure created to assess health-related quality of life in the general population. The SF-36 measures eight scales: physical functioning, role physical, bodily pain, general health, vitality, social functioning, emotional role, and mental health. Component analyses showed that there are two distinct concepts measured by the SF-36: a physical dimension, represented by the Physical Component Summary (PCS), and a mental dimension, represented by the Mental Component Summary (MCS).
*Cardiovascular Diet Questionnaire (CDQ-2)*: This CDQ-2 is validated against the reference method (7-day dietary history) and with biomarkers including plasma contents of saturated fatty acids (SFA), unsaturated fatty acids (UFA), UFA/SFA ratios and plasma folate concentration was used as a biomarker of the intake of fruits and vegetables [38]. It consists of 17 closed-ended questions designed to capture the main sources of the relevant nutrients.
*Motivation Scale towards Health-Oriented Physical Activity (EMAPS)*: The EMAPS is an 18-item scale designed to measure self-determined motivation toward physical activity [39]. It measures 6 dimensions of motivation: intrinsic motivation, identified regulation, integrated regulation, introjected regulation, external regulation, and amotivation.
*Preference for and Tolerance of Exercise Intensity* Questionnaire (PRETIE-Q): The PRETIE-Q is a 16-item scale designed to measure the preference for and tolerance of exercise intensity [40].
*The Physical Activity Regulation Scale (PARS)*: The PARS is a 14-item scale designed to measure behavioural regulation tactics used to manage actions after the formation of a physical activity intention. It comprises four dimensions: (a) proactive regulation, (b) reactive regulation, (c) social monitoring, and (d) self-monitoring [41].
*The Basic Need Satisfaction Scale* : The Basic Need Satisfaction Scale is 15-item scale designed to measure the need for autonomy, the need for competence, and the need for relatedness [42].
*The Interpersonal Behaviors Questionnaire (IBQ)*: The IBQ is a 24-item scale designed to measure the behaviors of the Adapted Physical Activity (APA) teacher. It comprises 6 dimensions: autonomy support, autonomy hindering, competence support, competence hindering, relatedness support, and relatedness hindering [43].

